### ***Study Measures***

Frailty will be measured based using validated criteria, and defined as an abnormality in 3 or more of 5 markers [1]: 1) low physical activity, by self-report using the International Physical Activity Questionnaire short form, 2) exhaustion, by self-report using a score of 2 or 3 on either of two exhaustion items from the Center for Epidemiologic Studies Depression Scale (CES-D), 3) weight loss, defined as a loss of 3 kilograms in the prior 3 months, 4) weak grip strength, using a hand-held dynamometer and based on age- and gender-based normative values, and 5) slow gait speed, based on a cutoff of 3.2 seconds or more to complete a 3-meter walk.

Perioperative complications will be prospectively graded and recorded using the modified Accordion scale [9, 10].

Pancreatic ductal adenocarcinoma (PDAC) Clinical Features: Additional clinical disease characteristics will be determined based on laboratory studies (albumin, prealbumin, c-reactive protein, creatinine, bilirubin, serum CA 19-9).

Demographic factors will include age, sex, race/ethnicity, place of residence, and presence of a primary caregiver.

Comorbidity will be determined prospectively using the Adult Comorbidity Evaluation-27 (ACE-27), a validated grading system that is predictive of prognosis in other cancer populations.

Symptom burden and quality of life (QOL) will be assessed using the Functional Assessment of Cancer Therapy-Hepatobiliary (FACT-Hep) quality of life and symptom index.

Physical functioning measures and exercise capacity: PROMIS SF v1.0 – Physical Function and 5x sit-to-stand test and 6-minute walk test

Lean body mass as measured by Slice-o-matic version 5.0.

Treatment side effects and fatigue: Participants will complete 2 items from the FACT-Hep daily, included on exercise logs. These items include GP5 ("I am bothered by side effects of treatment") and H17 ("I feel fatigued").

Physical activity will be measured using both objective monitoring and self-report.

Objective physical activity: Participants will undergo 2 weeks of objective monitoring using Actigraph GT3X accelerometers during each phase of neoadjuvant therapy (chemotherapy and/or chemoradiation and the preoperative recovery period) to measure total, light, and moderate-to-vigorous physical activity.

Self-reported physical activity: Participants will report physical activity using the IPAQ short form (administered as part of the frailty assessment) and in daily exercise logs.

Social support for exercise will be measured using the Social Support for Exercise Scale.

Neighborhood walkability for exercise will be measured using subscales E, F, G, and H from the Neighborhood Environment Walkability Survey – Abbreviated (NEWS-A). NEWS-A subscales will be administered to measure walkability for exercise in each neighborhood/area in which a patient lives during preoperative therapy.

Qualitative interviews will be conducted with a subsample of patients who have completed the exercise program. The purpose of these interviews is to examine program satisfaction and influences and outcomes related to adherence during the preoperative exercise program. Specifically, we seek to understand factors that may have motivated patients to exercise, differences in and barriers to adherence during different treatment phases, perceived physical and emotional benefits from exercise, program satisfaction, and suggestions for program improvement.

All patients who have completed the preoperative exercise program will be considered for enrollment on this protocol. Following pre-operative restaging appointments (for patients who do not undergo surgical resection) or discharge from MD Anderson after surgical resection (approximately 3-4 weeks after surgical resection) patients who are deemed interview candidates will be called by phone (by [name], a PhD candidate in kinesiology and Graduate Research Assistant in the Department of Surgical Oncology) to explain the purpose of interviews and steps that will be taken to analyze data and protect its confidentiality. During these calls, patients will be questioned regarding their interest in this interview, either at the time of the initial phone call or at a future time to be scheduled. Structured interviews will last approximately 30 minutes and will be audio-recorded using Microsoft Lync software. Audio files will be transcribed verbatim in Microsoft Word. De-identified, transcribed interviews will be managed using QSR Nvivo 10 software and analyzed for emergent themes by [name] and an additional PhD Kinesiology student with experience in qualitative data analysis. Interviews will be coded for emergent themes (first independently by each coder, then convergently as a coding pair) using a constant comparison approach. This approach allows for the

development of explanations through patterns but also allows coders to utilize theory and prior knowledge or research to answer research questions [11].

We aim to recruit roughly equal numbers of male and female participants and participants who met/exceeded or did not meet baseline recommendations for walking and resistance exercise. However, we recognize that differences in interest and availability can affect recruitment, and we may have imbalances in these proportions. Recent qualitative research studies examining influences and outcomes related to physical activity among cancer survivors have reached saturation of themes after interviewing five [12] and nine [13] participants. Ten of the 20 patients enrolled in the original 2014-0702 prehabilitation protocol underwent surgery, and we expect approximately 50% of the 50 patients who have enrolled or will enroll in the current (revised) protocol to undergo surgery. Therefore, we will have access to approximately 35 patients who are possible candidates for this study. We expect to conduct approximately 12-15 interviews among this group. Qualitative analysis of interview transcripts will occur on a rolling bases, however, and we will end recruitment and cease interviewing upon reaching saturation of qualitative themes.

The following is a list of interview topics and questions:

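### Interviews meant to explain barriers to adherence are open only to patients who completed the program, a term left undefined; separately, the candidate count of 35 omits unresected patients whom the contact procedure includes

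*Protocol*

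**What the plan says.** All of the main text is in the protocol for 2014-0702, section VII, under Study Measures (qualitative interviews).

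- **Who is interviewed.** "Qualitative interviews will be conducted with a subsample of patients who have completed the exercise program". The restriction is then repeated: "All patients who have completed the preoperative exercise program will be considered for enrollment on this protocol".
- **Why.** Among the aims is to understand "differences in and barriers to adherence during different treatment phases".
- **When patients are called.** "Following pre-operative restaging appointments (for patients who do not undergo surgical resection) or discharge from MD Anderson after surgical resection". Patients without resection therefore have their own contact point.
- **How many candidates.** Half of the first cohort, 10 of 20, had an operation. For the revised design the text reads: "we expect approximately 50% of the 50 patients who have enrolled or will enroll in the current (revised) protocol to undergo surgery". The conclusion drawn is: "Therefore, we will have access to approximately 35 patients who are possible candidates for this study".
- **How many interviews.** About 12–15, ending when themes are saturated. Two published studies that saturated at five and nine participants are cited in support.
- **Balance sought.** Roughly equal numbers by sex, and by whether baseline recommendations for walking and resistance exercise were met. Imbalance is accepted as possible.

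The opening of section VII defines adherence by phase, as at least 60% of the prescribed exercise time. No section defines completion of the program.

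**The concern.** A question about barriers is best put to those whom the barriers stopped as well as to those who carried on. The eligibility sentence admits only patients who completed the program, so a patient who discontinued because of toxicity, travel or lack of support cannot be sampled under the rule as written. The resulting themes would describe obstacles that patients managed to live with, and could understate those that ended participation. The stopping rule does not correct this, because saturation among completers carries no information about discontinuers.

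The interviews are meant to yield suggestions for improving the program and an account of how adherence differs between phases. A selected set of accounts could mislead that work. Because completion is undefined, staff also cannot tell whether a patient who gave up exercise during chemotherapy but later came to restaging may be called.

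The size of the candidate pool raises a second, smaller question, because the count and the contact procedure describe different groups.

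**Working it through.** **1. Frame against purpose.** This part is a comparison of text, not arithmetic.

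| Element | What the protocol sets | Consequence |
|---|---|---|
| Eligibility | Completers only, stated twice | Discontinuers cannot be selected |
| Purpose | Barriers to adherence, by phase | Discontinuers are directly relevant |
| Completion | Not defined | Eligibility of partial participants is unclear |
| Adherence | At least 60% of prescribed time in a phase | A separate measure; a patient can be non-adherent and still reach the end |
| Contact point | After restaging or after surgical discharge | Resection is not required |

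The frame therefore excludes discontinuers. It does not exclude low exercisers who reach the end of preoperative therapy.

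**2. The stated candidate count.** Inputs, all from Study Measures: 10 resected of the first 20 patients, and about 50% of the 50 patients under the revised design expected to have surgery.

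Candidates = 10 + 0.50 × 50 = 10 + 25 = 35.

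This reproduces the stated figure exactly, and only resected patients enter the sum.

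**3. The count on the group the contact procedure describes.**

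- Enrolled under both designs: 20 + 50 = 70.
- Not in the count: 70 − 35 = 35, all of them unresected.
- Planned interviews as a share of the counted pool: 12/35 = 34% to 15/35 = 43%.
- Planned interviews as a share of all enrolled: 12/70 = 17% to 15/70 = 21%.

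The 70 is a ceiling. Under Initial Assessment of Exercise Tolerance, some enrolled patients can be excluded before starting the intervention, and others may withdraw. The protocol gives no rate for this. If 50% to 100% of the 70 were eligible and reachable (an assumption), the pool would be 35 to 70.

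**4. What cannot be computed.** The protocol gives neither a discontinuation rate nor a completion rate, so the number of interviews that discontinuers would otherwise contribute cannot be derived from it.

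**The case against.** The strongest reply is that the frame may be wider than it looks. The program runs for the whole of preoperative treatment, and calls are timed by restaging or discharge, not by how much the patient exercised. On that reading, completing means reaching the end of the preoperative period, and someone who did very little in one phase can still be interviewed. Questions about how exercise changed between phases also need patients who passed through more than one phase. The sampling aim includes patients who did not meet baseline recommendations. Barriers are examined elsewhere too: in the two-weekly calls to all participants, in daily items on side effects and fatigue, and in the social support and walkability scales modelled against adherence in each phase. The interviews appear in no objective or endpoint.

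Much of this stands, and it rules out stronger conclusions that a reader might infer:

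- **That everyone who stopped exercising goes unheard.** Completion and adherence are separate, so non-adherent patients who reach the end remain eligible.
- **That section VII's remark on chemotherapy shows dropout.** It reports that patients seem less compliant in that phase, which is lower adherence, not leaving the program.
- **That half the patients are shut out.** The 35 missing from the count are unresected patients, whom the contact procedure covers. Resection status is not exercise status, and the figure is an estimate of availability, not an eligibility rule.

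The core point is not answered. The balance on baseline recommendations operates within the completer group, and may refer to activity before the program. The two-weekly calls use a list of screening questions and the scales are quantitative, so neither replaces the planned thematic analysis. If reaching the end of preoperative therapy is what was meant, the protocol needs to say so, and that reading still omits patients who left the program before then.

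**Conclusion.** The point holds in limited form. By the stated rule, patients who discontinued cannot be interviewed about barriers to adherence, and the undefined term leaves the edge of the group to judgement. The direction of the selection is clear, but its size cannot be stated because no discontinuation rate is given. The conclusion rests on reading the eligibility sentence as written.

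Separately, the count of about 35 is arithmetically right for resected patients but does not match the contact procedure. Correcting it can only enlarge the pool, to at most 70.

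Both matters concern an exploratory component. A reader might infer that the choice of phase for future trials is compromised, but section VII bases that choice on measured adherence per phase. The primary feasibility endpoint is unaffected. The wording should still be changed, because the repair is cheap and the interviews would otherwise miss a group central to one of their stated questions.

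**What to change.** 1. Redefine the interview frame in both eligibility sentences as patients who started the exercise program, whether or not they completed it or underwent resection, unless they withdrew consent to contact. Eligibility then no longer depends on the undefined term.
2. Within the planned 12–15 interviews, purposively include some patients who discontinued or who were non-adherent in at least one phase, using the adherence definition already in section VII. Do not declare saturation until some of them have been interviewed. A separate saturation rule for this group is not advised: with five and nine interviews cited for saturation, it could push the total above the plan.
3. Restate the candidate pool on the same frame, with a ceiling of 20 + 50 = 70 less exclusions and withdrawals, so that the count and the contact procedure agree.

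The cost is protocol wording. The planned number of interviews and the telephone procedure stay as they are. Some discontinuers will decline, so a few more calls will be needed.

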**A. Past exercise experience**

- Please describe your experience with aerobic exercise (like walking) prior to starting on our exercise program.
- Please describe your experience with strengthening exercise (like weight training) prior to starting on our exercise program.
- How did your past exercise experience affect your participation in this exercise program?

**B. Motivation to exercise**

- What motivated you to exercise during this program?
  - Potential probing questions:
    - What roles did diagnosis or goals for treatment play in motivating you to exercise during this program?
    - What roles did your family or friends play in motivating you to exercise during this program?
- Did your motivation to exercise change over the course of this program?
- How would you describe your motivation to exercise now that the program is finished and you've had surgery?

**C. Perceived exercise on the program**

- Did you feel like you were able to exercise enough during this program?
- How did your ability to exercise change from [modify as appropriate] chemo to chemotherapy and to preoperative rest?

**D. Barriers to exercise**

- Please describe any factors that made it difficult for you to exercise during this program.
  - Potential probing questions:

- Describe the role that scheduling or travel related to preoperative treatments played in your ability to exercise during this program.
- What aspects of your support system or resources at home made it difficult for you to exercise?
- What additional types of support or resources helped you exercise or exercise more?
- Did these factors change at all from [modify as appropriate] chemo to chemotherapy and to preoperative rest?

#### **E. Facilitators of exercise**

- Please describe any factors that made it easy for you to exercise during this program.
  - Potential probing questions:
    - What aspects of the program made it easy for you to exercise?
    - What aspects of your support system or resources at home made it easy for you to exercise?
- Did these factors change at all from [modify as appropriate] chemo to chemotherapy and to preoperative rest?

#### **F. Perceived outcomes**

- How do you think participating in this program and exercising during your preoperative therapy may have benefitted you?
  - Potential probing questions:
    - How did participating in this program affect the support you felt you had during your preoperative treatments?
    - How did participating in this program affect you physically?
    - How did participating in this program affect you emotionally?
    - How did participating in this program affect your ability to tolerate therapy?
    - How has the exercise program affected your recovery following surgery? [OR] How do you expect the exercise program to affect your recovery following surgery?

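### The only lead question on perceived outcomes in the interview guide presupposes benefit, and no listed question asks directly about unwanted effects

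*Protocol*

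**What the plan says.** The qualitative interviews are described in section VII under Study Measures of the prehabilitation protocol: "The purpose of these interviews is to examine program satisfaction and influences and outcomes related to adherence during the preoperative exercise program". The aims that follow narrow the outcome part to "perceived physical and emotional benefits from exercise, program satisfaction, and suggestions for program improvement". On format, the protocol states: "Structured interviews will last approximately 30 minutes". About 12 to 15 are expected, and interviewing ends once no new themes appear.

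The guide lists topics A to G. Topic F, headed Perceived outcomes, has a single lead question: "How do you think participating in this program and exercising during your preoperative therapy may have benefitted you". Five follow-up questions come under the label "Potential probing questions". They cover support, physical state, emotional state, tolerance of therapy and recovery from surgery. Two examples are "How did participating in this program affect you physically" and "How did participating in this program affect your ability to tolerate therapy".

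**The concern.** A lead question sets the frame for its topic. One that asks how a program helped invites the patient to search for benefits, and a patient who felt none, or felt worse, has to step outside the question to say so. Because topic F is the only place where the guide asks what the program did to the patient, this framing carries into the perceived-outcome themes.

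Two features of the plan give the wording more weight. The two-weekly calls under Adherence/compliance include teaching on why exercise is beneficial, so patients reach the interview already primed in that direction. And recruitment to the interviews stops at saturation, which could be judged complete on benefit themes before an unwanted-effect theme has been sought.

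At stake is the balance of one set of qualitative themes in a pilot that is meant to guide the focus of later studies. Perceived drawbacks are part of what such studies would want to know.

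**Working it through.** The point rests on wording, so no arithmetic applies. The check has three steps.

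**1. Every topic in the guide, read for direction.**

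| Topic | What it asks | Direct question on an unwanted effect? |
|---|---|---|
| A | Exercise experience before the program | No |
| B | Motivation, and whether it changed | No |
| C | Whether the patient could exercise enough, and how ability changed by treatment phase | No, but decline can be reported |
| D | What made exercise difficult | No; it asks what hindered exercise, not what exercise caused |
| E | What made exercise easy | No |
| F, lead question | How the program helped | No; one direction only |
| F, five probes | How the program affected five areas | No; neutral verb, harm not named |
| G | Satisfaction, what was enjoyed, what to change | No, but criticism can be voiced |

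Result: topic F has 1 lead question, framed as benefit. All 5 of its probes are neutral and none names harm. Across A to G, no question asks directly about an unwanted effect.

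**2. The guide against the stated purpose.** The purpose statement uses the undirected word outcomes. The specific aim keeps only one side: "perceived physical and emotional benefits from exercise". The lead question in F follows the narrowed aim. So the guide and the aim agree with each other, and both are narrower than the purpose. The guide treats influences in both directions, with barriers in D and facilitators in E. Outcomes have no such pair.

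**3. The rest of the study.** Under Adherence/compliance, staff telephone every two weeks and screen for exercise intolerance. Under Emergency contacts, there is a route for acute musculoskeletal injury and cardiopulmonary distress. Under Study Measures, patients answer two FACT-Hep items daily, one on treatment side effects and one on fatigue. Negative experience is therefore recorded elsewhere, although the two daily items do not ask whether exercise was the cause.

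**The case against.** The strongest reply is that the plan does what it set out to do. It names perceived benefits as an aim, and topic F asks about perceived benefits. The interviews are exploratory, concern outcomes linked to adherence, and are not a safety instrument. The lead question is hedged with *may*, and the five probes use a verb without direction. The probe on tolerating therapy openly invites a report that exercise got in the way of treatment, and the one on physical effects invites pain or exhaustion. Topic D would naturally bring out both as well.

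Much of this stands. There is no contradiction between the aim and the question, and the probes soften the framing whenever they are used. What does not follow is that the narrow aim justifies the narrow question, since both fall short of the broader purpose given just before the aim. The probes are also optional, come after the leading question and never name a negative effect.

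A reader might infer more than the document supports:

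- *The wording cannot be varied.* The interviews are called structured, but the guide is introduced as a list of topics and questions. It contains places marked for modification, an either/or alternative in topic F and probes that are only potential.
- *The interviews cannot hear of pain or exhaustion.* The neutral probes and topics C, D and G can bring these out indirectly.
- *Harm goes unmonitored.* The telephone calls, the emergency route and the daily items show otherwise.
- *A chance of missing an unwanted effect can be stated.* That would need its frequency and the share of patients who would not mention it unasked. The document gives neither.

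**Conclusion.** The point holds as a minor weakness of design. The one lead question on perceived outcomes presupposes benefit, no listed question asks directly about unwanted effects, and the themes from topic F will be tilted accordingly. The tilt is confined to that topic in a secondary qualitative component. It does not affect the adherence rates by treatment phase on which feasibility is judged.

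The direction of the tilt rests on the ordinary premise that a leading question influences what is volunteered. Its extent is unknown and depends on how consistently the interviewer uses the optional probes. It is a one-sided choice of wording, not an inconsistency in the plan and not a gap in safety monitoring.

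**What to change.** Make three small edits:

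1. Reword the lead question in topic F so that it is open in both directions, for example: *How, if at all, did taking part in the program and doing the exercises before surgery affect you, for better or for worse?*
2. Add one standard probe, put to every interviewee, on any unwanted effect of the exercise or the program.
3. In the aims under Study Measures, widen *benefits* to *benefits and unwanted effects*, so that aim, purpose and guide agree.

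The cost is a change of text in the guide and the aims. It needs no added staff or visits and should fit within the planned interview length. The one drawback is that any interviews already held will have used the present wording. Record which wording each interview used, and take it into account when the topic F themes are reported.
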